#### **14.2.8 HIV-specific immune response**

HIV-specific immune responses will be measured at timepoints as specified in the Schedule of Procedures (Appendix A1). A volunteer will be considered to have a positive response if he/she has at least one positive test result prior to HIV infection. Fisher's exact test will be used to test for any difference in the response rate between intermittent or daily FTC/TDF and placebo recipients. Assuming a 10% HIV-specific immune response rate in the combined control group, this study will have about 83% power to detect an increased response rate due to intermittent PrEP if the true response rate is 50% in the intermittent FTC/TDF group.

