#### *Study summary*

The study will allow for collection of important data on the feasibility of an intermittent/daily PrEP regimen in HIV discordant couples, and it will directly compare adherence and intracellular drug levels in daily and intermittent PrEP recipients. It will also evaluate the relationship between drug adherence, sexual behaviour and intracellular drug levels with an intermittent PrEP regimen. Specifically, this study will use timed plasma and intracellular drug levels after a witnessed dose and MEMS adherence data to model drug levels. This model can explore relationships between adherence and intracellular drug levels to determine if intracellular drug levels can be used as a surrogate adherence measure. In addition it will evaluate the relationship between adherence to an intermittent PrEP regimen and timing of sexual activity to estimate what proportion of sexual events may be 'protected' by intermittent PrEP. The pilot will use objective MEMS adherence measurement and evaluate the feasibility of newer adherence measurements such as hair sampling and plasma drug levels. The pilot will also evaluate the feasibility of using either IVR or SMS to collect sexual activity data in an African setting. It will allow study teams and communities to prepare for potential subsequent larger trials of intermittent PrEP. The pilot study is not sized to evaluate efficacy. If the pilot shows this intermittent PrEP regimen to be safe, feasible in terms of adherence, and to achieve intracellular drug levels similar to daily PrEP, this data could be used to design a larger phase 2 study with one or more intermittent PrEP regimens. The goal of such a trial would be to provide bridging data if daily PrEP regimens are found to be effective or to prepare for efficacy or non-inferiority trials of intermittent versus daily PrEP.

Investigation of immune responses associated with FTC/TDF will also be evaluated in the pilot study. The proportion of volunteers on FTC/TDF with HIV-specific immune responses will be assessed at 2-3 time points and compared to responses in volunteers assigned to placebo. Immune responses may be correlated with risk behaviour and host factors, such as HLA type. As noted above, very few HIV infections are expected to occur during the study, so correlation of HIV-specific immune responses and protection from infection or attenuation of disease progression will not be possible until a larger study is conducted.

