**6.2 Randomization Visit for HIV-uninfected volunteers**

*Prior to the randomization, research centre personnel will:*

- Answer any questions about the study
- Review interim medical history (including concomitant medications)
- Review screening safety laboratory data.
- Review the Informed Consent Document with the volunteer.
- Perform a symptom directed physical examination including vital signs (pulse, respiratory rate, blood pressure and temperature), and any further examination indicated by history or observation.
- Conduct an HIV risk behaviour assessment
- Conduct HIV pre-test counselling.
- Collect blood and specimens for all tests as indicated in the Schedule of Procedures (Appendix A1).
- Perform a pregnancy test for all female volunteers and obtain results prior to randomization.
- Conduct HIV risk reduction counselling and family planning counselling (for women)
- Conduct HIV post-test counselling

*After the randomization, research centre personnel will:*

- Collect Adverse Events and Serious Adverse Events
- Distribute investigational product with MEMS TrackCap
- Conduct adherence counselling
- Distribute SIM card or cell phone, if needed, for IVR or SMS
- Conduct IVR or SMS instruction

The volunteer will be assigned to a treatment arm (FTC/TDF or placebo) in a blinded fashion according to the instructions specified in the Study Operations Manual.

The investigational product will be distributed as specified in section 8.4 Distribution of Product.

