## **7.9 Swab Collection of mucosal secretions**

Swabs collecting mucosal secretions (to determine antibody secretion) will be used by the volunteers, after instruction, at the screening visit (see Section 7.2.). All specimens will be handled according to the procedures specified in the Study Operations Manual. In the event of an abnormal laboratory value, volunteers

may be asked to have an additional sample collected at the discretion of the principal investigator or designee.

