**12.2. Follow Up After Discontinuation of Further Administration of Investigational Product**

Volunteers, in whom further administration of investigational product are discontinued due to adverse events, will be followed until the adverse event resolves or stabilizes or up to the end of the study, whichever comes last. These volunteers will not participate in the Final Visit / Week 24 Visit. Volunteers who are discontinued for any reason will not be replaced.

HIV infected individuals who have received investigational product will be followed for an additional two visits after discontinuing investigational product to assess for the development of drug resistance mutations. If drug resistance is detected and determined to be related to study participation, further follow-up will be determined by the Safety Review Board.

Follow-up of pregnant volunteers will be done as specified in Section 10.6.

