| Hep BsAg and STI screening: urine for gonorrhoea and chlamydia; blood for syphilis; additionally for females vaginal swab for trichomonas, Candida vaginitis & bacterial vaginosis .
+ Swab to collect mucosal secretions for antibody secretion. | X      |       |     |     |       |            |        |       |           |       |             |           |           |
| Haematology (CBC) (+ plasma storage)                                                                                                                                                                                                                 | X      |       |     |     | X     |            | X      |       | X         |       | X           |           |           |
| Clinical Chemistry (creatinine, creatinine clearance, pancreatic amylase † , serum phosphate, aspartate transferase (AST), alanine transferase (ALT), total bilirubin                                                                     | X      |       |     |     | X     |            | X      |       | X         |       | X           |           |           |
| Urine dipstick +/- urinalysis                                                                                                                                                                                                                        | X      |       |     |     |       |            |        |       |           |       |             |           |           |
| HIV test                                                                                                                                                                                                                                             | X      | X     |     |     | X     |            | X      | X     | X         | X     | X**         | X**       |           |
| Pregnancy Test (all female volunteers)                                                                                                                                                                                                               | X      | X     |     |     | X     |            | X      | X     | X         |       |             |           |           |

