| Hair samples for adherence assessment                                                                                                                                                                                                                |        |       |     |     |       |            | X      |       | X         |       |             |           |           |
| Drug plasma and intracellular level testing                                                                                                                                                                                                          |        |       |     |     | X††   | X          | X      | X     | X         | X     | X           | X         |           |
| PBMCs (antibodies and cellular response against HIV antigens, intracellular drug levels, serum and plasma storage)                                                                                                                                   |        | X     |     |     | X     |            | X      | X     | X         | X     | X           | X         |           |
| Sample for HLA typing and related testing                                                                                                                                                                                                            |        | X     |     |     |       |            |        |       |           |       |             |           |           |
| CD4+ count, HIV viral load, p24 antigen, HIV genotyping, viral tropism assay, HIV sequencing                                                                                                                                                         |        |       |     |     |       |            |        |       |           |       | X           |           |           |

ET = Early Termination

HIV f/u 1 and HIV f/u 2 = Additional visits for HIV infected individuals after discontinuing investigational product to characterize infection and assess for the development of drug resistance mutations.

†Screening visit only

††Blood specimens for plasma and intracellular drug levels collected before and approx. 2 hours after witnessed administration of investigational product as part of the single-dose, timed pharmacokinetic study at Week 4 visit

\*Focus group/individual interview will take place as soon as possible after the final study visit.

\*\*If needed to confirm HIV diagnosis

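### The immune-responder rule in Section 14.2.8 has no start point, so pre-drug positives count as responses in every group and dilute the comparison with placebo

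*Protocol*

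**What the plan says.** Section 14.2.8 defines the endpoint: "A volunteer will be considered to have a positive response if he/she has at least one positive test result prior to HIV infection". The sentence before it fixes when: "HIV-specific immune responses will be measured at timepoints as specified in the Schedule of Procedures (Appendix A1"). The analysis is Fisher's exact test of intermittent or daily FTC/TDF against placebo. The power statement is about 83% for a 10% response rate in the combined control group and 50% in the intermittent FTC/TDF group.

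In Appendix A1 the relevant blood row, "PBMCs (antibodies and cellular response against HIV antigens, intracellular drug levels, serum and plasma storage"), is marked at Weeks 0, 4, 8, 12, 16 and 24. Section 6.2 lists specimen collection among the steps before randomization. Only after randomization do staff "Distribute investigational product with MEMS TrackCap".

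The Appendix A1 entry "Swab to collect mucosal secretions for antibody secretion" is marked in the screening column alone. Section 7.9 agrees: "Swabs collecting mucosal secretions (to determine antibody secretion) will be used by the volunteers, after instruction, at the screening visit".

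The study summary in Section 3.7 says that responses on FTC/TDF "will be assessed at 2-3 time points and compared to responses in volunteers assigned to placebo", which is fewer time points than Appendix A1 marks.

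**The concern.** The responder rule has an end bound, HIV infection, but no start bound. It does not require a negative baseline or a change from baseline. A volunteer who is already reactive at Week 0 is therefore a responder whatever happens afterwards. The mucosal assay can add only pre-drug positives, because its single specimen is taken at screening. Reactivity at entry is conceivable in this population: Section 5.2.3 requires an HIV-infected partner not using ART and recent unprotected sex.

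Two things are at stake. Each group's reported response rate would mix pre-existing reactivity with reactivity that arose on study. Positives common to both groups would also narrow the contrast that the test is meant to detect. The Week 0 sample that could separate the two is already being drawn.

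**Working it through.** **Inputs from the protocol.** Groups of 24 (intermittent FTC/TDF) and 24 (combined placebo), Section 14.1. Rates of 50% and 10%, and Fisher's exact test, Section 14.2.8. Section 14.2.8 gives no significance level, so two-sided 0.05 is assumed, as stated for the condom-use power in Section 14.2.6.

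**Assumed input.** The protocol gives no rate of positivity before drug. Call it *b*, the same in both groups by randomization, and take 5%, 10% and 20% as a range.

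**Step 1: reproduce the plan's figure.** Sum the binomial probabilities over all 25 × 25 outcomes with a two-sided Fisher p-value of 0.05 or less. The result is 83.4%, against about 83% stated. The figure is correct for its inputs.

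**Step 2: treat 10% and 50% as post-drug rates.** Under the written rule the response rates become

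- placebo: *b* + (1 − *b*) × 0.10
- FTC/TDF: *b* + (1 − *b*) × 0.50

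If Week 0 positives are excluded instead, the rates return to 10% and 50%, with about 24 × (1 − *b*) volunteers per group.

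| *b* | Placebo, as written | FTC/TDF, as written | Power as written (24 vs 24) | n per group, Week 0 negatives | Power, Week 0 negatives |
|---|---|---|---|---|---|
| 5% | 14.5% | 52.5% | 74.5% | 23 | 81.1% |
| 10% | 19.0% | 55.0% | 66.5% | 22 | 78.6% |
| 20% | 28.0% | 60.0% | 53.0% | 19 | 70.9% |

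Exclusion costs a few volunteers and still gives more power in every row.

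**Step 3: treat 10% and 50% as already including pre-drug positives.** With *b* = 5%, the rates among Week 0 negatives are

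- placebo: (0.10 − 0.05) / 0.95 = 5.3%
- FTC/TDF: (0.50 − 0.05) / 0.95 = 47.4%

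With 23 per group, power is 90.8%, against 83.4% under the written rule.

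**Step 4: type I error.** With 24 per group and equal true rates of 10%, 26.5%, 40% and 47%, the test rejects in 1.7%, 2.6%, 2.7% and 2.9% of trials. A common background positivity leaves the test conservative.

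**The case against.** The strongest reply is that the power claim is not wrong. Section 14.2.8 first defines a response and then assumes 10% and 50%. Read in that order, these are rates of the endpoint as defined, background included, and 83% holds by construction. This stands. The losses in Step 2 depend on the other reading, and no value of *b* is in the protocol. The case for a baseline rule survives because it gains power under either reading.

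A reader might infer that the rule credits FTC/TDF with a spurious effect. The documents do not support that. The same rule applies to randomized placebo, and Step 4 shows no type I inflation.

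A reader might also infer that six rounds of testing pile up assay false positives; for example, an assumed 2% per round gives 1 − 0.98^6 = 11.4%. Six assay rounds are not established. The Appendix A1 row marks a shared collection that also serves drug levels and storage. Section 3.7 speaks of two or three time points, and Section 9.2.2 leaves assay selection to the Laboratory Analytical Plan and a possible prioritization by available specimens. The false-positive rate and independence between rounds are assumptions too, and 11.4% is in any case close to the 10% already assumed for controls.

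Section 12.2 says of volunteers stopped for adverse events: "These volunteers will not participate in the Final Visit / Week 24 Visit". They have one fewer chance to test positive, but nothing in the protocol lets one size the effect, so the point does not rest on it.

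Finally, dropping Week 0 positives departs from Section 14.2, which bases all analyses on the modified intention-to-treat cohort. That is fair, and the fix keeps that analysis.

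**Conclusion.** The point holds as a defect of definition. As written, Week 0 and screening-swab positives count as responses in all groups. This blurs the per-group rates and dilutes the Fisher comparison. It does not bias that comparison toward FTC/TDF, and it does not make the 83% figure wrong for 10% against 50% with 24 per group.

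The size depends on assumptions. If 10% and 50% are post-drug rates and 5% to 20% of both groups are positive before drug, power falls to between about 75% and 53% as written, against 81% to 71% among Week 0 negatives. If the rates already include 5% pre-drug positives, exclusion lifts power from 83% to about 91%.

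Severity is minor. Section 5.1.2 lists this among the other endpoints and Section 9.2.2 calls the immune evaluations exploratory. No primary endpoint depends on it, although Section 19.0 does plan to describe immune responses in the primary manuscript.

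**What to change.** In Section 14.2.8, define a responder as a volunteer who is negative at Week 0 and has at least one positive post-randomization result in the same assay, before any HIV infection. Report Week 0 positives and screening-swab positives separately by group, and state that the screening swab does not count toward response. Keep the analysis of the full modified intention-to-treat cohort as a sensitivity analysis. State which visits are assayed for immune response, so that the two or three time points of Section 3.7 agree with Appendix A1. State also whether 10% and 50% refer to this new definition.

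The cost is protocol or analysis-plan wording and a few volunteers leaving the main denominator: about 1, 2 or 5 of 24 per group at 5%, 10% or 20% pre-drug positivity. No visit or specimen is added. Requiring positives at more than one visit is a separate choice between sensitivity and specificity; its power has not been worked out, and this point does not need it.

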## **15.0 QUALITY CONTROL AND QUALITY ASSURANCE**

To ensure the quality and reliability of the data gathered and the ethical conduct of this study, a Study Operations Manual has been developed.

Regular monitoring will be performed according to ICH-GCP as indicated in Section 17.3.

An independent audit of the study may be performed, at the discretion of the sponsor.

By signing the protocol, the Principal Investigators agree to facilitate study related monitoring, audits, IRB/IEC review and regulatory inspection(s) and direct access to source documents. Such information will be treated as strictly confidential and under no circumstances be made publicly available.

## **16.0 DATA AND BIOLOGICAL MATERIAL**

All data and biological material collected through the study shall be managed in accordance with the Clinical Trial Agreement. Distribution and use of those data will be conducted by agreement of both parties.

The computerized raw data generated will be held by the DCC on behalf of the sponsor. The study research centre will also hold the final data files and tables generated for the purpose of analysis. Principal investigators or designees will have access to the clinical study database with appropriate blinding.

## **17.0 ADMINISTRATIVE STRUCTURE**

The Principal Investigator will be responsible for all aspects of the study at the study research centre.

### **17.1 Safety Review Board (SRB)**

The SRB will oversee the progress of the study. The SRB will consist of independent clinicians/scientists/statisticians who are not involved in the study. Investigators responsible for the clinical care of volunteers or representative of the sponsor may not be a member of the SRB.

However, the SRB may invite the Principal Investigators or designees and a sponsor representative to an open session of the meeting to provide information on study conduct, present data or to respond to questions.

The review of study data by the SRB will take place after approximately 25% of volunteers have been followed for 2 months and may also be specifically requested (see Section 17.1.2 Indications for discontinuation of administration of investigational product in all volunteers). Enrolment will continue during this review.

#### **17.1.1 Content of Interim Review**

The SRB will be asked to review the following data:

- A blinded listing of all severe clinical adverse events, independent of relationship to the Investigational Product, and
- A blinded listing of all severe laboratory adverse events confirmed on retest, independent of relationship to the Investigational Product, and
- A blinded listing of all Serious Adverse Events, independent of relationship to the Investigational Product.

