#### **17.1.2 Indications for discontinuation of administration of investigational product in all Volunteers**

If 2 or more of the volunteers participating in this study develop an SAE judged definitely or probably related to the investigational product, the Principal Investigators or designees and the sponsor will request a review by the SRB. The study will be suspended pending a review of all safety data by the SRB. The study may be unblinded at the discretion of the SRB.

Following this review, the SRB will make a recommendation to the Sponsor and the Principal Investigators regarding the continuation of the study.

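### The one scheduled safety board review is specified as blinded listings only, so as written it does not supply the FTC/TDF-versus-placebo comparison; a closed-session table by arm would be a minor, cheap improvement

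*Protocol*

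**What the plan says.** Section 17.1 sets up an SRB of "independent clinicians/scientists/statisticians who are not involved in the study". Sponsor representatives and investigators responsible for volunteers' care cannot be members, though they may be invited to an open session. The one scheduled review takes place "after approximately 25% of volunteers have been followed for 2 months and may also be specifically requested"; the requested review is the one described in section 17.1.2. Enrolment continues meanwhile.

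Section 17.1.1 gives the content of the interim review as three items:
- "A blinded listing of all severe clinical adverse events, independent of relationship to the Investigational Product"
- "A blinded listing of all severe laboratory adverse events confirmed on retest, independent of relationship to the Investigational Product"
- "A blinded listing of all Serious Adverse Events, independent of relationship to the Investigational Product"

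Section 17.1.2 covers the requested review. Its trigger is "If 2 or more of the volunteers participating in this study develop an SAE judged definitely or probably related to the investigational product". The study is then suspended while the SRB reviews all safety data, and in that context the protocol adds: "The study may be unblinded at the discretion of the SRB".

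Three other sections matter. Section 7.12 has the DCC prepare the randomization schedule, and blinds product but not regimen. Section 13.3 has the DCC send interim reports to the sponsor, the principal investigator and the SRB. Section 7.13 allows emergency unblinding of an individual, restricted to those treating that volunteer.

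**The concern.** The placebo groups let drug-related abnormalities be told apart from background illness. The SRB is the body best placed to use that contrast during the trial, because it is independent of both sponsor and clinic. Yet the scheduled review is defined by blinded listings, and the sentence on unblinding is attached to a different review with a narrow trigger.

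Severe non-serious events, severe laboratory events and SAEs judged only possibly related do not meet that trigger, however many occur. An excess of such events on FTC/TDF could be in the listings without the SRB being shown which arm it came from. Showing the SRB the arms need not unblind the sponsor, investigators or site staff.

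**Working it through.** **Where by-arm data could reach the SRB.** No figure in the protocol is in dispute, so the main check is of the text.

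| Place | What it provides | FTC/TDF v placebo for the scheduled review? |
|---|---|---|
| 17.1.1 | three blinded listings | no |
| 17.1.2 | discretion to unblind after the SAE trigger | only in the triggered review |
| 13.3 | DCC interim reports, also sent to sponsor and principal investigator | not described as unblinded |
| 7.13 | emergency unblinding of one volunteer | not addressed to the SRB |
| 10.4 | SRB told of product-related SAEs | individual cases, no arm comparison |

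The protocol does not define a blinded listing. Since regimen is open, only the product contrast is hidden.

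**How narrow the trigger is.** Section 10.3 counts possibly related SAEs as product-related for expedited reporting; section 17.1.2 does not count them. For an assumed true rate p of qualifying SAEs on FTC/TDF, the chance that at least 2 of n treated volunteers have one is 1 − (1−p)^n − n·p·(1−p)^(n−1).

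| Assumed p | n = 48 (all FTC/TDF) | n = 12 (see next step) |
|---|---|---|
| 1% | 0.083 | 0.006 |
| 2% | 0.249 | 0.023 |
| 5% | 0.699 | 0.118 |
| 10% | 0.960 | 0.341 |

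The protocol gives no such rate, so the range is an assumption.

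**Volunteers behind the scheduled review.** Inputs: 72 volunteers (14.1), allocation 2:2:1:1 (5.2), 25% with two months of follow-up (17.1). 0.25 × 72 = 18. Split 2:2:1:1 this is 6, 6, 3 and 3, so 12 on FTC/TDF and 6 on placebo.

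The listings would also include later enrollees. If accrual is uniform over the anticipated 3 months (5.2.1; uniformity is assumed), 24 enrol per month. The 18th enters at 0.75 months, the review falls at 2.75 months, and 24 × 2.75 = 66 are enrolled (44 v 22). Their mean follow-up is 2.75/2 ≈ 1.4 months, or about 66 × 1.375 ≈ 91 person-months out of 72 × 4 = 288 planned on drug. Head counts alone would therefore mislead, and a table needs follow-up time.

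**What a by-arm table could show.** Power of a two-sided 0.05 Fisher test (excess on FTC/TDF), summed exactly over both binomials, with the 5% control rate that section 14.2.1 uses as its example:

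| Rate on FTC/TDF | 12 v 6 | 48 v 24 (full enrolment) |
|---|---|---|
| 20% | 0.3% | 32% |
| 30% | 3% | 71% |
| 50% | 30% | 99% |
| 75% | 85% | about 100% |

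With no placebo events at 12 v 6:
- Six events all on FTC/TDF have probability C(12,6)/C(18,6) = 924/18564 = 0.050. Adding the opposite tail (73/18564) gives a two-sided p of 0.054.
- Seven have probability 792/31824 = 0.025. Adding the opposite tail (408/31824) gives 0.038.

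So 7 of 12 are needed. Within one regimen (6 v 3), 5 of 6 are needed: C(6,5)/C(9,5) = 6/126 = 0.048, with no equally extreme table in the other tail. A table split only by regimen is weaker still, so a pooled FTC/TDF-versus-placebo line is needed.

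**The case against.** The strongest reply is that nothing is misstated. A blinded first look in a 72-person pilot, with unblinding held in reserve for related SAEs, is a coherent choice, and section 14.2.1 openly admits limited power for adverse events. That stands, and it is why this is a suggested improvement and not an error.

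Three stronger readings are tempting, and the protocol does not support them.
- A reader might infer that the SRB is barred from arm-level data. Section 17.1.1 says what the SRB will be asked to review; it does not forbid asking for more, and rules for the board may sit in a document not shown. What can be said is that the protocol provides no such data and states no such discretion outside section 17.1.2.
- A reader might infer that the scheduled review depends on investigators' causality judgements. It does not: all three listings are supplied whatever the attribution. The SRB is also told of product-related SAEs, including possibly related ones (10.3, 10.4), and the laboratory rules in section 12.1 work volunteer by volunteer without a between-arm comparison.
- A reader might infer that a by-arm table would have a good chance of exposing harm early. The power figures show otherwise.

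None of these safeguards supplies the randomized comparison. That narrow gap remains.

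**Conclusion.** The point holds as a minor one. The scheduled review, as specified, does not give the SRB the FTC/TDF-versus-placebo comparison, and the stated discretion to unblind belongs to a different review with a narrow trigger. The gain from closing the gap is modest: with about 12 v 6 volunteers at two months, a by-arm table supports clinical judgement and would show only very large imbalances.

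This rests on reading a blinded listing as one without product assignment, on the planned 72 volunteers and 2:2:1:1 allocation, and on the absence of any other provision in the protocol. The 66-enrolled figure additionally assumes uniform accrual. No conclusion follows that the trial's safety oversight is inadequate overall.

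**What to change.** Amend section 17.1.1 so that the DCC gives the SRB, in closed session only, the same three listings plus event counts, denominators and follow-up time by arm, shown pooled across regimens (FTC/TDF v placebo) and by regimen. State in section 17.1 that the SRB may unblind at any review, not only the one in section 17.1.2.

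Coding the arms A and B will not hide them, because 2:1 denominators reveal which is which. The table should therefore be treated as confidential to the SRB and kept separate from the interim reports that section 13.3 also sends to the sponsor and principal investigator. Sponsor, investigators and site staff stay blinded.

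The cost is one extra DCC table per review and a few lines of text, with no added visits or staff. The downside is that SRB members will see very small numbers by arm, so the table should carry a note that it informs judgement and is not a formal test.
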